#### Muscle strength and balance

Prior to muscle testing, subjects will be familiarised with all assessment procedures. In addition, a warm-up consisting of aerobic activity and stretching will be undertaken. Dynamic concentric muscle strength for the leg press, chest press and seated row undertaken in the program will be measured using the one repetition maximum (1-RM) method. The 1-RM is the maximal weight an individual can move through a full range of motion without change in body position other than that dictated by the specific exercise motion
[36]. A Neurocom Smart Balancemaster (Neurocom, OR, USA) will be used to assess standing balance. This device measures ground reaction force to track whole body centre of pressure and a tilting visual field and support platform to separate the visual, somatosensory and vestibular balance sense of the patient. Falls self-efficacy will be determined using the Activities-Specific Balance Confidence scale. During the course of the intervention, all participants will record any falls that take place and submit monthly fall records to the investigators.

#### Objective measures of physical function

A battery of tests will be used to assess functional performance
[24,37]. Tests will be performed in triplicate (except for the 400-m walk which will be performed once) with sufficient recovery time between trials. The best performance on each test will be used in the analyses. The tests will be; 1) repeated chair rise, 2) stair climb, 3) 6-m backward tandem walk, 4) 6-m walk, usual and fast pace, and 5) 400-m walk. Performance in each test will be timed electronically using a Kinematic Measurement System (Fitness Technology, Australia)

#### Physical activity level and motivation

Self-reported physical activity will be assessed by the leisure score index from the Godin Leisure-Time Exercise Questionnaire. ActiGraph activity monitors (triaxial accelerometer, GT3X+, Actigraph, Pensacola, Florida) will be used to objectively assess physical activity levels and sedentary time over a 7-day period
[38]. A 6-item questionnaire will be used to assess the domain-specific sedentary behaviour.

The Theory of Planned Behaviour (TPB) is the most widely utilised behavioural framework when examining physical activity motivation in cancer survivors. Therefore, physical activity motivation will be assessed in accordance with the TPB. TPB constructs (affective and instrumental attitude, injunctive and descriptive norm, self-efficacy, perceived behavioural control, intention, and planning) will be assessed in accordance with established guidelines using standardised items
[39].

#### Health-related quality of life and psychological distress

Health-related QOL will be measured using the Medical Outcomes Study Short-Form 36 (SF-36), European Organisation for Research and Treatment of Cancer (EORTC) QLQ-C30 and EORTC QLQ-PR25 as well as a health history questionnaire. This validated instrument is an integrated system to assess QOL in cancer patients and has been extensively employed in clinical trials
[40]. The Brief Symptom Inventory-18 (BSI-18) will be used to assess psychological distress (Anxiety, Depression and Somatisation)
[21]. Higher somatization and anxiety as measured by the BSI-18 is associated with greater physical inactivity in cancer survivors
[21]. The Impact of Events Scale (IES) and the Memorial Anxiety Scale for Prostate Cancer (MAX-PC) will be used to measure cancer specific distress
[41,42]. A core self-evaluation questionnaire and lifestyle individual resilience scale will be used to assess core self-evaluation and three related aspects of resilience (individual, social–peers and social–family resources). Fatigue will be assessed using the Functional Assessment of Chronic Illness Therapy-Fatigue (FACIT-F) questionnaire. The FACIT-F is a 13 item scale commonly used to assess fatigue in cancer patients
[43] as well as cancer patients receiving exercise interventions
[44]. Items from the Pittsburgh Sleep Quality Index (PSQI) will be used to measure sleep quality
[45]. The PSQI is used to assess quality of sleep over a 1-month interval, and has been shown to be reliable and sensitive to change
[46].

### Exercise intervention

The intervention program will comprise resistance, aerobic and impact-loading exercises undertaken 3 times per week in an exercise clinic. The frequency of resistance and aerobic exercises will alternate weekly so two aerobic/impact loading and one resistance/impact loading sessions are performed in the first week and two resistance/impact loading and one aerobic/impact loading are performed in the subsequent week. Resistance training sessions will take approximately 60 minutes (this includes the warm-up and cool-down periods) and will be conducted in the Exercise Clinics at Edith Cowan University (ECU) in Perth and seven other partner sites in Western Australia: Perth; Mandurah; and Bunbury. We also have another site at the University of Newcastle where we have identical equipment and procedures. The programme will include exercises such as leg press, leg extension, leg curl, chest press, seated row, lat pulldown and bicep curl that target the major upper and lower body muscle groups, which we have used in a number of previous studies
[24,26,37,47] including men on ADT. To ensure the progressive nature of the training program, subjects will be encouraged to work past the specific repetition maximums (RMs) prescribed. The resistance will be increased by 5-10% increment for the next set/training session if the subject is able to perform more repetitions than the RMs specified during a set. Intensity will be manipulated from 6-12-RM (e.g. the maximal weight that can be lifted 6 to 12 times) using 1–4 sets per exercise. The aerobic component will include 25–40 minutes of cardiovascular exercise using various modes such as walking or jogging on a treadmill, cycling or rowing a stationary ergometer, or exercising on a cross training machine. Target intensity will be 60-85% estimated maximum heart (220–age) with individual heart rate watches (Polar Electra Oy, Finland) provided for each participant. In addition to the clinic training, participants will be encouraged to undertake twice weekly home-based training incorporating aerobic activity (e.g. walking, cycling) and a modified version of the impact-loading regimen (only including hopping, leaping and drop jumping) for the duration of the study. The impact-loading regimen will be performed a minimum of 3 times per week for the duration of the trial, in combination with the resistance and aerobic exercise. For the first 10 weeks, 2 rotations will be performed of skipping (30 sec), bounding over soft hurdles (13–16 cm), and drop jumping (10–15 cm). In the second 10-week period, hopping on one leg (10 times) will be added, leaping (10 times) will replace skipping, and 4 rotations of bounding (19–25 cm), drop jumping (20–25 cm), hopping, and leaping will be performed for the remainder of the programme. These activities result in substantial peak ground reaction forces ranging from 3.4 to 5.2 times body weight providing excellent stimulus to bone yet proven safe and accepted by older people
[48].

All exercise sessions will be conducted in small groups of up to 6–10, with participants exercising in pairs and under direct supervision to ensure correct technique and minimize the risk for injury. Each session will commence with a 10-minute warm-up comprising low-level aerobic activities such as walking and stationary cycling, as well as stretching and conclude with a 5-minute cool-down period of stretching activities. In order to reduce the possibility of boredom and overreaching the exercise program will be periodised by cycling emphasis on intensity and volume. Also, within sessions variations of circuit training and intermittent exercise sessions (intervals of high and low intensity exercise) will be introduced. The exercise program will be designed to provide optimal stimulus to the skeletal, cardiorespiratory and neuromuscular systems while maximizing compliance and retention. All participants will be asked to maintain customary physical activity and dietary patterns over the intervention period (apart from the programmed exercise). Physical activity and dietary intake will be assessed at baseline, 6 and 12 months. During the course of the study, participants will be required to maintain an activity log and record their recreational physical activities. Participants in the DE group will be contacted every 4 weeks to encourage them to maintain current physical activity levels and record their activities. Dietary intake, at the same time points as for physical activity, will be assessed using a 4-day dietary record. Dietary information will be derived using the FoodWorks software program.

### Calculation of sample size

Data from our 36-week study
[15] in prostate cancer survivors initiating ADT indicates that the standard deviation (SD) for change in our primary outcome of BMD equates to approximately 4.5% and 3.3%, for the hip and lumbar spine, respectively. With ADT, the annual loss is reported to be 2-8% at the spine and 1.8-6.5% at the hip
[49,50] and based on our 36-week data, we obtained an initial loss of 1.5% and 3.9% for the hip and lumbar spine, respectively. Therefore, we anticipate losses of approximately 1.5% and 3.5% at the clinically relevant fracture sites of the hip and spine. We anticipate a difference between the immediate and delayed exercise groups of approximately 2.5% at the hip and 4.5% at the lumbar spine, which would be clinically significant and substantially reduce the risk for fracture. A priori, 51 subjects per group will be required to achieve 80% power at an alpha level of 0.05 (two-tailed), and to demonstrate a difference between groups at each bone site at the end of the 6-month intervention. Previous experience in our exercise trials indicates an attrition rate of up to 20% over the course of the study period. Therefore, to adequately ensure that we have sufficient subject numbers at the end of the intervention, 124 subjects will be randomised in a ratio of 1:1 to the immediate and delayed exercise groups, respectively. A sample size of 124 will also provide us with sufficient power to detect differences in our secondary outcomes which all have larger effect sizes based on our previous research.

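### The 124 randomised do not quite cover the stated maximum attrition: at 20% loss, 62 per arm leaves 49.6, not the required 51; the effect on hip power is about one percentage point

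*Protocol article*

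**What the plan says.** All the figures are in the protocol article, Methods/design, under Calculation of sample size.

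- Requirement: "A priori, 51 subjects per group will be required", for 80% power at a two-sided alpha of 0.05.
- Inputs: the SD of change in BMD is "approximately 4.5% and 3.3%, for the hip and lumbar spine, respectively", and the expected between-group difference is "approximately 2.5% at the hip and 4.5% at the lumbar spine".
- Comparison that is powered: "to demonstrate a difference between groups at each bone site at the end of the 6-month intervention".
- Attrition: "an attrition rate of up to 20% over the course of the study period".
- Conclusion: "Therefore, to adequately ensure that we have sufficient subject numbers at the end of the intervention, 124 subjects will be randomised", allocated 1:1.

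Table 1 and the Subjects section confirm 62 per arm. The sections on measurements place the last assessment at 12 months, so the study period is twice as long as the interval to the powered comparison.

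**The concern.** The conclusion is presented as following from the requirement and the attrition figure, yet removing 20% from 62 leaves fewer than 51. To keep a required number after a proportion is lost, one divides by the proportion retained. The total of 124 is what results from multiplying 51 by 1.2 and rounding up. The article shows no inflation formula, so that explanation is an inference from the match.

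What is at stake is the assurance attached to 124. The hip sets the sample size, and the protocol wants a difference shown at each site, so any shortfall falls on the site with the least power to spare. Anyone who monitors dropout against the stated 20% would also be using a tolerance that the design does not have.

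**Working it through.** **Inputs** (all from Calculation of sample size, except the arm size, which is in Table 1 and Subjects): two-sided alpha 0.05 (z = 1.96); power 80% (z = 0.8416); hip difference 2.5%, SD 4.5%; spine difference 4.5%, SD 3.3%; attrition up to 20%; 62 per arm.

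**1. Reproduce the requirement.** Normal approximation, n per group = 2 × (1.96 + 0.8416)² × (SD/difference)².

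- Hip: 2 × 7.849 × (4.5/2.5)² = 50.9, rounded up to 51. This matches the protocol.
- Spine: 2 × 7.849 × (3.3/4.5)² = 8.4, rounded up to 9.

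The hip drives the number, and 51 is correct by this method.

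**2. Inflate for attrition.**

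- Dividing by the proportion retained: 51/(1 − 0.20) = 63.75, so 64 per arm, 128 in total. Check: 64 × 0.80 = 51.2, which meets 51.
- Multiplying by one plus the proportion lost: 51 × 1.20 = 61.2, so 62 per arm, 124 in total. This equals the stated figure.

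**3. What 124 leaves.**

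- At 20% loss: 62 × 0.80 = 49.6 per arm, or 99.2 in total against the 102 needed.
- Largest loss that still leaves 51 per arm: 1 − 51/62 = 17.7%.

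**4. Power for the hip** (difference 2.5%, SD 4.5%). The normal approximation is Φ[(2.5/4.5) × √(n/2) − 1.96]; the t-test column uses the noncentral t distribution.

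| Evaluable per arm | Loss from 62 | Normal approximation | Two-sample t test |
|---|---|---|---|
| 52.7 | 15% | 81.4% | 80.7% |
| 51 | 17.7% | 80.1% | 79.3% |
| 50 | 19.4% | 79.3% | 78.5% |
| 49.6 | 20% | 79.0% | 78.2% |

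By either method, going from 51 to 49.6 per arm costs 1.1 percentage points.

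**5. Power for the spine** at 49.6 per arm (difference 4.5%, SD 3.3%) is above 99.9% by both methods.

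**The case against.** The strongest reply concerns timing. The 20% is an upper bound and covers the whole study, whereas the powered comparison is at 6 months. If loss were spread evenly over the 12 months (an assumption; the article gives no 6-month rate), about 10% would be gone by 6 months. That would leave about 62 × 0.90 = 55.8 per arm, with hip power of 83.5% (normal) or 82.9% (t test). On that reading the design has room to spare. This limits the consequence, and it stands. It does not reconcile the figures, because the protocol itself ties the 20% to the numbers available when the intervention ends and offers no lower rate for that point.

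A second reply is that one percentage point is within the precision of the inputs, which the protocol calls approximate. With 49.6 per arm, an SD of 4.4% in place of 4.5% brings t-test power back to 80.0%. That also stands, and it bears on size.

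Two stronger readings are tempting and should be resisted.

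- A reader might infer that the trial fails to deliver its 80% hip power. The documents do not support that. The shortfall depends on more than 17.7% being lost in the first 6 months, which the protocol does not predict.
- A reader might add that 51 is itself too few, because a t test needs 52 per group for 80% (51.8 before rounding up). A normal-approximation sample size is common practice, and Statistical analysis does not make the t test the primary analysis: it lists t tests beside regression and repeated measures ANOVA or ANCOVA. Setting a t-test power of 78.2% against a requirement derived from the normal approximation would also overstate the effect of attrition, by mixing two methods.

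**Conclusion.** The attrition step is wrong as written. At the protocol's own upper bound, 124 randomised men leave 49.6 per arm, where 51 are required; 128 would be needed to cover that bound. The arithmetic is certain, since it uses only printed figures. That the cause was multiplication by 1.2 is likely but not shown.

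The size is minor: 2 men per arm, and 1.1 points of hip power at the full 20% loss (80.1% to 79.0% by the normal approximation, 79.3% to 78.2% by the t test). The spine is unaffected. These power figures assume the stated hip difference and SD, equal loss in the two arms, and a simple two-group comparison of change that uses only men measured at 6 months. No endpoint, analysis or conclusion of the trial depends on this point.

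**What to change.** Keep 124 and replace the assurance with a statement of what that number tolerates, for example:

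> Sixty-two per arm retains the required 51 per arm if attrition by 6 months is at most 17.7%. If the maximum of 20% were lost by then, about 50 per arm would remain, giving about 79% power (normal approximation; about 78% by t test) for a 2.5% hip difference with SD 4.5%.

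If the team has a lower attrition rate in mind for 6 months, stating it would settle the matter. If the full 20% bound is to be covered at 6 months, the number randomised would have to be 128.

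The cost of the recommended change is a short rewording and no extra participants. Its downside is that the stated power becomes slightly less favourable.

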### Statistical analysis

Data will be analysed using SPSS statistical software package and an intention-to-treat approach will be applied. Analyses will include standard descriptive statistics, Student’s *t* tests, correlation and regression, and two-way (group x time) repeated measures ANOVA (or ANCOVA as appropriate) to examine differences between groups over time. All tests will be two-tailed and an alpha level of 0.05 will be applied as the criterion for statistical significance.

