### Measurements

All measurements for primary and secondary endpoints will take place at baseline, 6 and 12 months. Additional blood measures, scans and questionnaires will also be undertaken at 3 months to track changes over time during the initial 6 months for bone formation and resorption markers. Body composition measures for muscle and fat mass will also be performed at 3-month intervals to track the trajectory of change in these outcomes.

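### The repeated measures ANOVA named beside intention-to-treat becomes a completer analysis if it is run on all three visits without imputation

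*Protocol article*

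**What the plan says.** The Statistical analysis section makes two commitments in consecutive sentences. The first is the principle: "Data will be analysed using SPSS statistical software package and an intention-to-treat approach will be applied". The second is a list of methods. It opens with "Analyses will include standard descriptive statistics, Student’s *t* tests, correlation and regression" and ends with "two-way (group x time) repeated measures ANOVA (or ANCOVA as appropriate) to examine differences between groups over time". The last item is the only one tied explicitly to group differences over time. No listed method is assigned to the primary endpoint (hip and spine areal BMD), and the section does not say which visits enter the ANOVA.

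Three other statements bear on this:

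- Measurements sets the visits: "All measurements for primary and secondary endpoints will take place at baseline, 6 and 12 months".
- Calculation of sample size fixes the powered time point, where the aim is "to demonstrate a difference between groups at each bone site at the end of the 6-month intervention".
- The same section expects loss: "Previous experience in our exercise trials indicates an attrition rate of up to 20% over the course of the study period". It does not divide that loss into before and after month 6.

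**The concern.** Classical repeated measures ANOVA needs a value at every level of the time factor and removes a subject listwise if one is missing. With baseline, 6 and 12 months as the levels, and nothing imputed, the analysed set is the men who completed month 12. That does not fit an unqualified intention-to-treat statement when up to a fifth of the men may leave.

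Two things are at stake. The first is precision, because primary-endpoint scans already taken at month 6 would be set aside. The second is validity. After month 6 the arms face different demands: the delayed arm starts clinic sessions three times a week, while the immediate arm has no formal intervention. Different dropout in that period is therefore plausible. If attendance at month 12 decides who counts at month 6, a randomised comparison is conditioned on a later event that may depend on arm.

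**Working it through.** **Inputs** (Calculation of sample size): SD of change 4.5% hip and 3.3% spine; anticipated difference 2.5% hip and 4.5% spine; two-sided alpha 0.05; power 80%; 51 per group needed; 62 per arm randomised; attrition up to 20%.

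**Step 1. Reproduce the plan's figure.** n per group = 2 × (1.960 + 0.842)² × (SD/difference)².
- Hip: 2 × 7.849 × (4.5/2.5)² = 50.9, so 51. This matches the plan. The exact t calculation gives 52.
- Spine: 2 × 7.849 × (3.3/4.5)² = 8.4, so 9.

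The hip drives the sample size, so the hip is where a loss of men matters.

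**Step 2. Men available.** Assume that 20% of each arm is lost by month 12, and let s be the unknown share of that loss that falls before month 6.
- Complete on all three visits: 62 × 0.80 = 49.6 per arm, whatever s is.
- With a 6-month scan: 62 × (1 − 0.20 × s) per arm.

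**Step 3. Hip power at 6 months.** Two-sample noncentral t, noncentrality = (2.5/4.5) × √(n/2), 2n − 2 degrees of freedom. At n = 49.6 the noncentrality is 2.77 and power is 78.2%.

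| Share lost before month 6 | 6-month scans per arm | Discarded per arm by listwise deletion | Power, all 6-month data | Power, three-visit completers | Points lost |
|---|---|---|---|---|---|
| 0 | 62.0 | 12.4 | 86.6% | 78.2% | 8.4 |
| 0.25 | 58.9 | 9.3 | 84.8% | 78.2% | 6.6 |
| 0.5 | 55.8 | 6.2 | 82.9% | 78.2% | 4.7 |
| 0.75 | 52.7 | 3.1 | 80.7% | 78.2% | 2.4 (from unrounded values) |
| 1 | 49.6 | 0 | 78.2% | 78.2% | 0 |

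Spine power is about 100% in every row.

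**Step 4. Bias, as an illustration only.** Assume that 20% of the delayed arm is lost, all of it after month 6, that the immediate arm loses nobody, and that the odds of leaving rise by a factor of 1.65 or 2.7 (log-odds slope 0.5 or 1.0) per SD of greater 6-month bone loss. The retained delayed-arm men then have a mean change above the full-arm mean by E[z(1 − p(z))]/0.80, where z is standardised change and p(z) the probability of leaving.
- Slope 0.5: shift 0.096 SD × 4.5 = 0.43. The hip difference becomes 2.5 − 0.43 = 2.07%.
- Slope 1.0: shift 0.173 SD × 4.5 = 0.78. The hip difference becomes 2.5 − 0.78 = 1.72%.

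With all 6-month scans kept, the difference stays at 2.5%. That follows by construction, because the illustration places no loss before month 6.

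**The case against.** The strongest reply is that the article never describes the analysis being criticised. It does not say that all three visits enter one ANOVA or that incomplete cases are deleted. A t test or ANCOVA at 6 months, an ANOVA on baseline and 6 months, or imputation before a three-visit ANOVA would each fit the wording, and each would keep the 6-month scans. The sample size itself reproduces from a simple two-sample comparison of change. Missing-data handling is also commonly left to a fuller document that is not shown, so its absence is no fault.

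Most of this stands. A reader might infer that the plan commits to analysing only men with all three visits, or that the text flatly contradicts itself. The document supports neither reading. What remains is narrower: the one method tied to differences over time, used in its ordinary way on the scheduled visits, works against the principle stated in the sentence before it. That is a problem with a method the article names, not a gap in detail.

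The objections on size also stand. The power cost can be zero, and 20% is an upper bound. The 78.2% is not purely an effect of the ANOVA: if all loss came before month 6, any method without imputation would have the same 49.6 per arm, fewer than the 51 required. That concerns how the sample size was inflated and is a separate matter. The dropout mechanism in Step 4 has no support in the document. If it acted equally in both arms, on change measured from each arm's own mean, the shifts would cancel and the difference would stay at 2.5%. A different mechanism could reverse the direction.

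**Conclusion.** The concern holds conditionally. If the named repeated measures ANOVA is run on baseline, 6 and 12 months without imputation, it is a complete-case analysis and does not honour the stated intention-to-treat approach for the powered 6-month contrast. With 20% lost by month 12, it discards between 0 and about 12 men per arm who have a 6-month scan and costs 0 to 8.4 points of hip power, depending on dropout timing that the article does not give. Spine power is essentially unaffected.

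Bias in the 6-month contrast is possible but not shown. The fall from 2.5% to about 2.1% or 1.7% at the hip rests on assumed slopes and on loss in the delayed arm only. Because the wording also permits analyses that keep the 6-month data, this is a should-fix point and not an established error.

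**What to change.** For the primary endpoint, replace the repeated measures ANOVA with a likelihood-based linear mixed model, available as MIXED in SPSS. Fit arm by categorical visit, baseline BMD as a covariate and an unstructured covariance over the post-baseline visits. Include every randomised man with any post-baseline value, in the arm to which he was randomised. Name the 6-month contrast as primary and take the 12-month contrast from the same model.

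The change needs no new data, visits or software, only revised analysis wording, settled before unblinding, and slightly more analysis work. Men with no post-baseline scan still contribute no outcome, so the missing-at-random assumption should be stated. The mixed model is not the only way to keep the 6-month scans: a 6-month ANCOVA, which the current wording allows, would also do so. The mixed model has the advantage of giving both time points from one analysis.
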